### 5.3 Escape medication (if applicable)

*Not applicable*

## **6. INVESTIGATIONAL PRODUCT**

**6.1 Name and description of investigational product(s)**

**6.2 Summary of findings from non-clinical studies**

**6.3 Summary of findings from clinical studies**

**6.4 Summary of known and potential risks and benefits**

**6.5 Description and justification of route of administration and dosage**

**6.6 Dosages, dosage modifications and method of administration**

**6.7 Preparation and labelling of Investigational Medicinal Product**

**6.8 Drug accountability**

**7. NON-INVESTIGATIONAL PRODUCT**

*Not applicable.*

- 7.1 Name and description of non-investigational product(s)**
- 7.2 Summary of findings from non-clinical studies**
- 7.3 Summary of findings from clinical studies**
- 7.4 Summary of known and potential risks and benefits**
- 7.5 Description and justification of route of administration and dosage**
- 7.6 Dosages, dosage modifications and method of administration**
- 7.7 Preparation and labelling of Non Investigational Medicinal Product**
- 7.8 Drug accountability**

## **8. METHODS**

### **8.1 Study parameters/endpoints**

Clinical interviews and self-report questionnaires assessing DSM-5-TR insomnia and prolonged grief symptoms will be administered at the start of the study. Insomnia and prolonged grief symptoms will be measured weekly for a period of 26 weeks using self-report questionnaires.

#### **8.1.1 Main study parameter/endpoint**

The primary aim is to assess the effect of CBT-I on prolonged grief symptoms. To assess this effect, prolonged grief symptoms will be measured weekly for a period of 26 weeks starting parallel to the waiting period and continuing through the treatment phase. The mean difference in symptom levels between the baseline phase (waiting period) and treatment phase will serve as the primary outcome.

#### **8.1.2 Secondary study parameters/endpoints (if applicable)**

The secondary aim is to assess the effect of CBT-I on insomnia symptoms in people with prolonged grief disorder. The analysis of the insomnia symptoms will be identical to the analysis of prolonged grief symptoms.

#### **8.1.3 Other study parameters (if applicable)**

Besides primary and secondary outcome measures, inclusion and exclusion criteria will be assessed next to sociodemographic and loss-related characteristics (age, gender, education level, kinship to the deceased, gender of the deceased, cause of death, expectedness of the loss).

### **8.2 Randomisation, blinding and treatment allocation**

Randomization will be used to determine the length of the waiting period (the baseline). We will use randomizer.org to generate a random list of 20 numbers ranging between five and 14, representing the possible number of weeks of the waiting period. Directly after completing the clinical interview, the participant will be allocated to the first available number on this computer-generated list. In case drop-out occurs a new number between five and 14 will be drawn and added to the end of the list.

### **8.3 Study procedures**

Recruitment of bereaved adults ( $\geq 18$  years) who lost a first-degree relative or partner will take place via localized Google AdWords advertisements and websites for organizations for bereaved persons, linking to a research website ([www.onderzoekrouw.nl](http://www.onderzoekrouw.nl)). Additionally, people who have participated in earlier studies and indicated an interest in future studies will be asked to visit the website. On the website, interested bereaved adults can access information about the study (see E1) and can provide informed consent on a secure online survey program, Qualtrics. After providing online informed consent (see E2), they will be requested to complete a screener for sociodemographic and loss-related characteristics, sleep disorders (ISI; Bastien et al., 2001; Holland Sleep Disorders Questionnaire; HSDQ; Kerkhof et al., 2013) and PGD (Traumatic Grief Inventory Self-Report Plus; TGI-SR+;

Lenferink et al., 2022).

People who meet the established cut-off values for insomnia disorder (ISI score >14) and prolonged grief disorder (TGI-SR+ score  $\geq 33$ , on the DSM5-TR items) based on screener results will be invited to meet online (via a secure online meeting program) or to visit the Heymans Institute of the University of Groningen for a clinical interview to assess PGD (Traumatic Grief Inventory-Clinician Administered, TGI-CA; Lenferink et al., 2023) and insomnia disorder (Structured Clinical Interview for DSM-5 Sleep Disorders, SCIDS; Taylor et al., 2018). The diagnostic criteria for PGD are intense yearning/longing for the deceased and/or preoccupation with thoughts or memories of the deceased, combined with three or more emotional, cognitive, and behavioral symptoms (DSM5-TR; American Psychiatric Association, 2022). The diagnostic criteria for insomnia disorder are experiencing problems falling and/or staying asleep at least 3 nights per week and for at least 3 months resulting in daytime dysfunction/distress (DSM5-TR; American Psychiatric Association, 2022).

Prior to the clinical interviews, participants will be provided with the study information letter once more (see E1) and an informed consent form (see E2). The clinical interviews will be conducted by a psychologist in training to become a registered healthcare psychologist under the supervision of a registered healthcare psychologist. When participants meet all inclusion criteria and none of the exclusion criteria, they can immediately start the waiting period for CBT-I.

Once the waiting period has started, participants will receive weekly questionnaires assessing prolonged grief (TGI-SR+) and insomnia symptoms (ISI). These weekly questionnaires will continue for 26 weeks covering both the baseline and intervention phase of the study.

Following the waiting period, participants will receive CBT-I following the standard Dutch protocol (Verbeek & van de Laar, 2023). CBT-I will be delivered by a psychologist in training to become a healthcare psychologist, supervised by a registered healthcare psychologist. CBT-I consists of 6-7 weekly individual, face-to-face sessions of 1-2 hours according to the Dutch CBT-I protocol (Verbeek & van de Laar, 2023). Depending on the location of the participant, these sessions can be held at the Heymans Institute or online using a video conference program. At four weeks post-treatment, a booster session will be planned to evaluate sleep health and, if necessary, repeat certain treatment components.

### Measures used during the study

- The Holland Sleep Disorder Questionnaire (HSDQ; Kerkhof et al., 2013) is a validated, Dutch, self-assessment questionnaire to screen for sleep disorders, such as insomnia disorder, sleep-related breathing disorders, and sleep-related movement disorders.
- The Traumatic Grief Inventory Plus (TGI-SR+; Lenferink et al., 2022) is a validated questionnaire that assesses all current symptoms of disturbed grief, including PGD as per ICD-11 and DSM5-TR. We will use the 12 items reflecting symptoms of DSM-5-TR PGD. We will use the original version, assessing symptoms over the past month, as well as an adapted version assessing symptoms over the past week.
- The Traumatic Grief Inventory Clinician Administered (TGI-CA; Lenferink et al., 2023) is an interview to assess all current criteria for disturbed grief, including PGD per ICD-11 and DSM-5-TR. We will use the 12 items reflecting symptoms of DSM-5-TR PGD.
- The Structured Clinical Interview for DSM5 Sleep Disorders Revised (SCISD-R; Taylor et al., 2018) is a well-validated clinical interview to assess DSM-5-TR sleep disorders, including insomnia disorder.

- The Insomnia Severity Index (ISI; Bastien et al., 2001) is a widely used and validated questionnaire that assesses insomnia severity. Items cover both day- and nighttime symptoms as well as worries about sleep. The ISI will be slightly adjusted to assess symptoms in the last week.

#### **8.4 Withdrawal of individual subjects**

Subjects can leave the study at any time without providing any reason if they wish to do so without any consequences.

##### **8.4.1 Specific criteria for withdrawal (if applicable)**

Not applicable

#### **8.5 Replacement of individual subjects after withdrawal**

If for any reason participants decide to withdraw from participation in the study before completing or during CBT-I, new participants will be included to ensure sufficient power for conducting the planned analyses.

#### **8.6 Follow-up of subjects withdrawn from treatment**

Participants who withdraw from the study will be invited to complete all assessments.

#### **8.7 Premature termination of the study**

If unexpected side effects or events occur that the researchers have not foreseen and are possibly associated with the proposed intervention, the study will be ended prematurely.

## **9. SAFETY REPORTING**

### **9.1 Temporary halt for reasons of subject safety**

In accordance to section 10, subsection 4, of the WMO, the sponsor will suspend the study if there is sufficient ground that continuation of the study will jeopardise subject health or safety. The sponsor will notify the accredited METC without undue delay of a temporary halt including the reason for such an action. The study will be suspended pending a further positive decision by the accredited METC. The investigator will take care that all subjects are kept informed.

### **9.2 AEs, SAEs and SUSARs**

#### **9.2.1 Adverse events (AEs)**

Adverse events are defined as any undesirable experience occurring to a subject during the study, whether or not considered related to the experimental intervention. All adverse events reported spontaneously by the subject or observed by the investigator or his staff will be recorded.

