**Nature and extent of the burden and risks associated with participation, benefit and group relatedness:**

The current study will be of minimal burden and negligible risk to participants. Exclusion criteria are used to minimize risks to participants. In addition to the clinical interview at the start of the study, participants will be asked to fill out 26 weekly questionnaires consisting of 19 multiple-choice questions (< 5 minutes to complete) for which they will receive 5 euros per assessment. These questionnaires will also be used as an evaluation of the treatment. Finally, participants will be asked to complete a follow-up questionnaire, three months after the last treatment session. This questionnaire will take no more than 5 minutes to complete and results in an additional payment of 50 euros.

There are minimal risks/burden associated with CBT-I. CBT-I is the gold standard treatment for insomnia worldwide, has been investigated in numerous studies, and is recommended in clinical practice (see: Riemann et al., 2023). Furthermore, CBT-I has been shown to be effective in people with comorbid psychiatric disorders (see also: Mijster et al., 2022)

An important component of CBT-I is stimulus control therapy. During stimulus control therapy participants are instructed to leave the bedroom when noticing they are not falling asleep and to return only when feeling sleepy. Furthermore, participants are instructed to refrain from any activity other than sleep and sex in the bedroom. For elderly mobility-impaired participants, getting out of bed during nighttime might increase the risk of falling. These participants are therefore not instructed to get out of bed. These participants will be instructed to remain in bed, and to do something none sleep related and relaxing such as listening to a podcast, or reading a magazine, in low-light conditions.

Another important component of CBT-I is sleep restriction therapy, in which patients are instructed to restrict their bedtimes to their average sleep time. Reducing sleep times could lead to certain risks. Specifically, this intervention is associated with mild short-term side effects such as performance impairment and reduced reaction times (Kyle et al., 2014).

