These side effects are similar to what is normally observed in insomnia patients. Therefore, for reasons of safety, participants are instructed to spend a minimum of 5 hours in bed each night and to refrain from driving a car or operating heavy machinery if they feel excessively sleepy during the early stages of sleep restriction therapy. Importantly, sleep restriction is a potent intervention technique that may lead to some side effects at first, but also leads to an amelioration of such experiences over time.

Additionally, minimal risks/burden are associated with the repeated measurement of symptoms of prolonged grief disorder and insomnia. This repeated measurement might elicit some negative feelings in participants. However, it is our experience from prior survey research among hundreds of bereaved adults, that they generally find it comforting to know that their grief can contribute to something positive, such as scientific knowledge. Nevertheless, to further reduce the risk of eliciting negative feelings, we will only use validated questionnaires applied successfully before in the bereaved population.

Finally, participants who still experience severe and disabling grief reactions (TGI-SR + score  $\geq 33$ , on the DSM5-TR items) at the 3-month follow-up will be offered the possibility of receiving CBT for prolonged grief disorder from a psychologist within the research team. CBT for prolonged grief disorder is the golden standard treatment for prolonged grief disorder and can be effectively delivered in person and online (e.g., Komischke-Konnerup et al., 2024; Wagner et al., 2020).

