### **11.4 Benefits and risks assessment, group relatedness**

A benefit of the current study is that it investigates a promising new approach to the treatment of prolonged grief disorder. Current evidence-based treatments for prolonged grief disorder have shown limited success rates, with no more than 50% of clients reporting clinically relevant improvement (for reviews: Doering & Eisma, 2016; Johannsen et al., 2019). Recent studies have suggested that insomnia symptoms might be causally implicated in the persistence of severe, disabling grief reactions (e.g., de Lang et al., 2023, 2024; Lancel et al., 2020). Insomnia therapy has shown promising effects in other stress and mood-related disorders such as depression (Gee et al., 2019) and post-traumatic stress disorder (Ho et al.,

2016) and a small pilot study has shown promising effects of insomnia therapy on prolonged grief symptoms in bereaved parents (Sveen et al., 2021). Therefore, it is likely that targeting insomnia symptoms in people with both prolonged grief disorder and insomnia disorder will reduce both insomnia and prolonged grief symptoms.

A benefit for participants in the study is that we will use CBT-I, the gold standard treatment for insomnia worldwide, which has been investigated in numerous studies, and is recommended in clinical practice (see: Riemann et al., 2023). While CBT-I has minimal risks, some components carry specific concerns. Stimulus control therapy, which involves leaving the bedroom if unable to sleep and using the bed solely for sleep and sex, may increase the risk of falls for elderly or mobility-impaired participants. To prevent this, such participants will not be instructed to leave the bed. Sleep restriction therapy, another CBT-I component, requires limiting time in bed to the average duration of sleep. Although effective, this approach can cause short-term side effects like reduced reaction times and performance impairments, common among those with insomnia. To enhance safety, participants will spend at least five hours in bed each night and will be advised to avoid driving or operating heavy machinery if they feel excessively sleepy during the therapy's early stages. Over time, these side effects typically diminish as the therapy takes effect.

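### Section 9.2.1 records only volunteered or observed adverse events, with no planned prompt for the harms the protocol itself names

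*Protocol*

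**What the plan says.** Protocol section 9.2.1 uses a broad definition: "Adverse events are defined as any undesirable experience occurring to a subject during the study, whether or not considered related to the experimental intervention". The recording rule that follows is narrower: "All adverse events reported spontaneously by the subject or observed by the investigator or his staff will be recorded".

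Elsewhere the protocol names particular harms. On sleep restriction, the Summary (burden and risks) says "this intervention is associated with mild short-term side effects such as performance impairment and reduced reaction times". It tells participants to "refrain from driving a car or operating heavy machinery if they feel excessively sleepy during the early stages of sleep restriction therapy". On stimulus control it says "For elderly mobility-impaired participants, getting out of bed during nighttime might increase the risk of falling", and it does not instruct that group to leave the bed. Section 11.4 repeats these risks and adds: "Over time, these side effects typically diminish as the therapy takes effect".

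The regular data collection is described in the Summary as "26 weekly questionnaires consisting of 19 multiple-choice questions". Section 8.3 limits the content to the TGI-SR+ and the ISI. Section 5.2 adds a question about additional care, at the start and after completion. Section 9.6 classes the risk as negligible and plans no DSMB and no interim safety analysis.

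**The concern.** The protocol foresees specific harms but relies on participants to volunteer them. Falls at night and sleepiness at the wheel happen at home or on the road, so the observation half of the rule will rarely catch them. A participant who has been told to expect some tiredness may also see no reason to report it.

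Two things are at stake. The first is what a low count would mean: it could reflect few events or few reports, and the data could not separate the two. The statements that risk is minimal and that side effects fade would gain little support from this trial. The second is any before-and-after reading of adverse events. Opportunities to mention an event differ sharply between the waiting period and the weeks that follow. An excess after treatment start could come from contact alone, and the absence of an excess would be just as hard to read.

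The decisions in sections 8.7 (premature termination) and 9.1 (temporary halt) also depend on events coming to light.

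**Working it through.** The plan states no figure on this point, so there is none to reproduce. The check sets named harms against planned prompts, then counts scheduled contacts.

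**1. Named harms against planned prompts**

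| Harm named (Summary; 11.4) | Planned prompt |
|---|---|
| Impaired performance, slowed reactions | None as an adverse event; the ISI covers daytime symptoms (8.3) and may overlap |
| Excessive sleepiness, driving or machinery | None |
| Night-time fall | None |

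The measures in section 8.3 and the other parameters in section 8.1.3 include no adverse event checklist, sleepiness scale or falls question.

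**2. Items on the weekly form**

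- Total questions: 19 (Summary).
- TGI-SR+ items: 12 (section 8.3).
- Remainder: 19 − 12 = 7.

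The ISI is the only other instrument named for this form. The protocol does not state its item count, so giving all 7 to the ISI is an inference. In either case no item is assigned to adverse events.

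**3. Scheduled staff contacts**

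- Baseline: 5 to 14 weeks, questionnaires by e-mailed link (section 3). Contacts scheduled: 0.
- Weeks after baseline: 26 − 14 = 12 to 26 − 5 = 21.
- Contacts after baseline: 6 + 1 = 7 to 7 + 1 = 8 (weekly sessions plus one booster).
- Contacts per week after baseline: 7/21 = 0.33 to 8/12 = 0.67.
- Weeks after baseline without a scheduled contact, at one contact per week: 12 − 8 = 4 to 21 − 7 = 14.

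**4. What a zero count could show**

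With 0 of 20 participants affected and every event captured, the one-sided 95% upper limit on risk is 1 − 0.05^(1/20) = 0.139, or 13.9%. If only a share c of affected participants is captured, the same calculation bounds risk × c, so the limit on the risk itself is about 0.139/c. The documents give no basis for c, and none is assumed here. The limit is above 13.9% whenever capture is incomplete. Better capture moves c towards 1; it cannot bring the limit below 13.9%, which is set by the sample size.

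**The case against.** Six counter-arguments deserve weight.

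- **A reader might infer that participants are never asked about these harms. The text does not support that.** The protocol is silent on what therapists ask. Sessions are weekly, individual and 1 to 2 hours long, and bedtimes are adjusted on the past week's reported sleep, so sleep is discussed during the period of greatest risk. The treatment manual is not at hand. What stands is that the protocol requires no prompt.
- **A reader might infer that a planned comparison is biased. It is not.** Using participants as their own controls concerns the TGI-SR+ and ISI. No adverse event comparison by phase is planned, and the difference in capture is inferred from the contact schedule. What stands is that such counts could not be compared if anyone tried.
- **Mitigation exists.** The group named as at risk of falling is not told to leave the bed, time in bed has a floor, and advice on driving is given. This lowers the expected risk but does not record whether the measures worked.
- **The named harms arise in treatment, when contact is weekly.** This is correct, and it makes missing prompts the main gap, followed by the 4 to 14 later weeks without a scheduled contact.
- **The trial does not set out to prove safety.** Also correct: its objectives are efficacy only, and serious events have their own reporting route in section 9.2.2. This limits the importance of the point.
- **Added questions could conflict with other text.** The Summary and section 11.4 commit to validated questionnaires only, and section 8.7 ends the study if unforeseen, possibly related events occur. Both are fair objections. They argue against an open health question and for fixed items on foreseen effects, with the exception stated.

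**Conclusion.** The point holds as an inexpensive improvement in safety ascertainment. Followed as written, section 9.2.1 is likely to under-record the harms the protocol names, because nothing prompts for them and most occur out of staff sight. A low count would be weak support for the minimal-risk statement. Adverse event counts before and after treatment start would not be comparable, with 0 scheduled contacts against 7 to 8.

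The size of the under-recording cannot be estimated from the documents. The conclusion rests on two assumptions: that the protocol describes all planned prompts, and that scheduled contact affects how often people volunteer events. If the treatment manual already requires the therapist to ask, the gap shrinks to the baseline and the contact-free weeks afterwards.

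It would go too far to conclude that the efficacy result is affected or that the trial is unsafe. The primary test uses TGI-SR+ scores only, and nothing here bears on how treatment is given.

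**What to change.** 1. In section 9.2.1, change the rule to solicited plus spontaneous recording.
2. Add two fixed yes/no items on the past week to the weekly form: a fall; excessive sleepiness while driving or operating machinery. Ask them in all 26 weeks, so that baseline serves as each participant's comparator. Add no open free-text item.
3. Have the therapist ask the same two questions at each session and at the booster.
4. Report both descriptively by phase, as a rate per participant-week. With 20 participants the planned total is 20 × 26 = 520 participant-weeks. For the comparison by phase, use the weekly form, whose schedule is the same in both phases; list therapist-elicited reports separately.
5. Change the stated number of questions from 19 to 21.
6. State in the Summary and section 11.4 that these safety items are an exception to the commitment to validated questionnaires. Section 8.3 already adapts the TGI-SR+ and ISI to a one-week recall.
7. State that the items concern foreseen effects, so a positive answer does not by itself fall under the section 8.7 wording on unforeseen events.

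Cost: two extra questions on a form of under 5 minutes, a short descriptive table, more minor adverse events to record, and two unvalidated items. Treatment instructions, sample size and the primary analysis do not change.
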